### Primary Outcome Variables

Alcohol and illicit drug use will be assessed using scales from the monitoring the future study**,** including lifetime, past 6 months, and past 30 days of illicit drug and alcohol use (past 1 and 3 months, and number of days in the last month) [31]. Participants will be asked about their use of marijuana, lysergic acid diethylamide, phencyclidine, mushrooms, cocaine, crack, ecstasy, stimulants, and prescription drugs without a physician’s prescription. Participants will be asked about the circumstances during which they use substances; for example, larger parties versus more intimate gatherings. We will also collect urine samples at baseline, after the intervention, and at 3 months and 6 months after the intervention to test for metabolites of methamphetamines, cocaine, ecstasy, marijuana, and opiates using the Integrated E-Z Split Key Cup II—5 Panel (Innovacon Laboratories), which can detect drugs from 1 to 4 days after use, except for chronic marijuana use, which can be detected for up to 30 days [32].

Sexual risk behaviors, partners and HIV risk, and protective behaviors will be assessed using scales adapted from the Healthy Young Men’s (HYM) Cohort Study [4,30]. Participants will be asked about their lifetime and recent sexual experiences (past 1 and 3 months), including insertive or receptive oral sex, insertive or receptive vaginal sex, and insertive or receptive anal sex. Specifically, participants will be asked to report the number of times they engaged in each type of sexual activity and the gender and sexual orientation of their partners. They will be asked about their sexual activity for different partner types (eg, primary, consistent casual, and casual) that they might have had in the past 3 months. They will be asked about the frequency of condom use and about their most frequent sexual activities. Finally, participants will be asked if they had ever and recently (past 1 and 3 months) exchanged sex for money, drugs, food, clothes, or other necessities. Condom use behaviors will be assessed by the Condom Use Self-Efficacy Scale: the 15-item Condom Use Self-Efficacy Scale measures condom use self-efficacy using a 5-point Likert scale.

HIV and STI testing and prevention behaviors and HIV status will be assessed using existing scales developed for use with African American YMSM [30], including participants’ self-reported HIV testing history and self-reported HIV status [4,30]. We will test for HIV using the INSTI HIV-1 or HIV 2 antibody test.

Participants will be asked to undergo a rapid test for HIV at baseline and 6-month follow-up assessments; participants with preliminary positive results will be referred to a confirmatory test, and those who seroconvert will be linked to HIV care. Participants will also self-collect rectal specimens for *Neisseria gonorrhoeae* and *Chlamydia trachomatis* nucleic acid amplification testing (Hologic) at baseline and at the 6-month follow-up. To ensure a smooth linkage to the care process, those with positive results will be referred and treated at a clinical partner site according to the CDC and Los Angeles County guidelines. Furthermore, we will use scales developed in prior research to assess knowledge and attitudes about PrEP and PEP and to measure adherence to PrEP for those reporting its use [33].

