**Methods:**

Through partnerships with community members and community-based organizations, we will further strengthen and refine YM-AIM to include 3 new components: biomedical HIV prevention strategies (pre-exposure prophylaxis and postexposure prophylaxis); HIV and sexually transmitted infection (STI) testing and HIV care referral, drug screening, and drug treatment referral; and a youth mentoring component. We will recruit African American YMSM, aged 18 to 24 years, into 2 working groups; each group will consist of 6 to 8 members and will convene on a weekly basis, and each meeting will focus on one specific YM-AIM topic. This feedback will be used to further refine the intervention, which will then be evaluated for its feasibility and acceptability. Intervention outcomes include drug use in the past 30 days and 3 months, alcohol use, condomless sex, number of sex partners, and increasing condom use intention, condom use self-efficacy, HIV and STI testing recency and frequency, and linkage to care.

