### Tracking and Retention

A tracking protocol developed for longitudinal research with African American YMSM [30] was used to maintain contact with the study participants. This protocol involves collecting and maintaining current contact information from participants, including addresses, emails, phone numbers, and social media handles. The research staff will contact the participants once a month to maintain current contact information. Participants will receive a US $5 incentive for their monthly check-in with research staff.

During phase 3, Y2Prevent will be pilot tested with 30 African American YMSM in 3 groups, each with up to 10 participants. All participants will be screened for eligibility and, if eligible, will be presented with the study description, asked to provide informed consent, and complete a baseline assessment. Pilot group participants will also be informed that their participation and feedback will determine the appropriateness of the intervention for African American YMSM and will be used to further develop and refine Y2Prevent. Participants will receive up to US $570 for participating in all components of the Y2Prevent pilot group, which includes 7 group sessions, 4 data collection periods including HIV and STI and substance use screens, the LifeWorks mentoring component, and monthly check-ins.

The pilot groups will be executed in sequential order so that the experiences from the first group can be used to adapt and further refine the intervention before it is pilot tested with the second group. Feedback from the first group will be used to adapt and refine the intervention for the second group, and feedback from the second group will be used to further adjust the intervention and test with a third pilot group. All pilot group sessions will last from 1.5 to 2 hours and will be held weekly for 7 consecutive weeks. A process evaluation will be performed throughout the pilot groups to document these experiences and to identify barriers and facilitators with respect to implementing Y2Prevent with our target group.

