### Measures

Evaluation of the intervention’s primary outcomes will involve administering a web-based self-report survey to participants at 4 time points: at baseline; after the intervention; and at 3 months and 6 months following completion of the intervention. The survey was administered via the internet using Qualtrics XM software. Evaluation of the acceptability and feasibility of Y2Prevent will be assessed through individual session satisfaction surveys administered immediately after each session and through an exit interview that will take place upon completion of Y2Prevent.

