### Data Analysis Plan

The pilot study will include 30 participants who will participate in 4 assessments (before the intervention, after the intervention and 3 and 6 months after the conclusion of the intervention). Data related to feasibility, acceptability, and adherence will be summarized as means and proportions with 95% CIs by the assessment period. Pre- to postintervention changes at different intervals will be evaluated using generalized linear mixed models; a subject-level random intercept will be specified. Estimates of changes at each postintervention assessment will be calculated, along with 95% CIs. Data will be summarized to identify any systematic differences in pilot outcomes to inform future large-scale randomized clinical trials. Furthermore, qualitative data from the exit interviews will be thematically assessed for positive or negative sentiments regarding participation in Y2Prevent.

Procedures for cleaning and screening data will include identifying and rectifying missing data and logical errors. Descriptive analyses will consist of univariate analyses, including SD, range, and value; patterns of correlation and covariance checks for multicollinearity; and identification of outliers and data distributions. Variables will be transformed as needed to reduce the effects of valid outliers or violations of normality.

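### At the immediate post-intervention survey, the 3-month recall items reach back before session 1, so that contrast understates change; the 1-month items do not have this problem

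*Protocol article*

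**What the plan says.** All references are to the protocol article.

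- **Programme length** (Tracking and Retention): the pilot group sessions "will be held weekly for 7 consecutive weeks".
- **Survey times** (Measures): the self-report survey is given "at baseline; after the intervention; and at 3 months and 6 months following completion of the intervention".
- **Drug and alcohol windows** (Primary Outcome Variables): "including lifetime, past 6 months, and past 30 days of illicit drug and alcohol use (past 1 and 3 months", together with the number of days of use in the last month.
- **Sexual behaviour windows** (same section): "lifetime and recent sexual experiences (past 1 and 3 months". Activity by partner type is asked only for partners "that they might have had in the past 3 months".
- **Outcome windows named in the abstract** (Methods): "drug use in the past 30 days and 3 months".
- **Contrasts** (Data Analysis Plan): "Estimates of changes at each postintervention assessment will be calculated, along with 95% CIs", from a generalized linear mixed model with a subject-level random intercept.

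Nothing in the article limits the first postintervention contrast to the 1-month items, and nothing resets recall to the time since the previous survey.

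**The concern.** A recall item can show a change after session 1 only to the extent that its window lies after session 1. Here two of the windows, 3 months and 6 months, are longer than the programme. A 3-month answer given straight after session 7 mixes weeks before the intervention with weeks during it. If the baseline survey is taken close to session 1, the same calendar weeks are counted in both the baseline and the post value.

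This pulls the baseline-to-post change in those items towards zero. It touches a named outcome, since the abstract lists 3-month drug use. It also touches partner-type activity, for which 3 months is the only stated window. The Data Analysis Plan says the pilot results are to inform later large randomized trials, so an early change estimate that is too small because of the window alone could mislead whoever uses it.

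**Working it through.** The article gives no overlap, effect-size or power figure, so there is nothing to reproduce. The check is window arithmetic.

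**Inputs**
- Window W: 30 days, 91 days (3 months) or 182 days (6 months), from Primary Outcome Variables.
- T, days from session 1 to the survey. Seven weekly sessions span 42 days from first to last, or 49 days as seven full weeks (Tracking and Retention). The gap from session 7 to the post survey is not stated. I assume T = 42 to 63, with 49 as the central value; 63 is a survey two weeks after the seventh full week. A wait between baseline and session 1 does not alter these shares; only a later post survey does.

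**Step 1. Share of the window before session 1** = max(0, W − T)/W

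| Window, at the post survey | T = 42 | T = 49 | T = 63 |
|---|---|---|---|
| 30 days | 0 | 0 | 0 |
| 3 months | 49/91 = 54% | 42/91 = 46% | 28/91 = 31% |
| 6 months | 140/182 = 77% | 133/182 = 73% | 119/182 = 65% |

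**Step 2. Later follow-ups.** These are timed from completion. With completion at day 49, the 3-month follow-up is at day 49 + 91 = 140 and the 6-month follow-up at day 49 + 182 = 231.
- 3-month window: 91 is less than 140, so 0% at both follow-ups.
- 6-month window: (182 − 140)/182 = 42/182 = 23% at the 3-month follow-up (49/182 = 27% if completion is dated to day 42), and 0% at the 6-month follow-up.

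**Step 3. Share of a true change in rate that the post contrast shows.** This assumes stable behaviour before session 1 and T = 49.
- Immediate change at session 1: 49/91 = 54% for 3 months and 49/182 = 27% for 6 months. Over T = 42 to 63 the 3-month share is 42/91 = 46% to 63/91 = 69%.
- Linear build-up over the 49 days: half of that, 24.5/91 = 27% and 24.5/182 = 13%.
- 30-day window: 100% for an immediate change. For a linear build-up the window covers days 19 to 49, so the average is (19/49 + 1)/2 = 69%.

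**Step 4. Yes/no items (illustration).** Assume Poisson episodes, a rate halved from session 1, T = 49 and 30.4 days per month.
- At 0.25 episodes a month, the chance of any use in 3 months is 0.527 at baseline, 0.421 at the post survey, and 0.312 if the whole window were at the halved rate. The contrast shows (0.527 − 0.421)/(0.527 − 0.312) = 49% of the difference.
- At 1 episode a month the values are 0.950, 0.888 and 0.776, and the share is 36%.

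**Step 5. Urine screens.** Primary Outcome Variables gives detection of 1 to 4 days, and up to 30 days for chronic marijuana use. Both are shorter than 42 days.

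**The case against.** The strongest reply is that the arithmetic is right but the reach is narrow and the consequence small. Several parts of it stand.

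- **Not every primary behavioural outcome.** A reader might infer that the first change estimate for every such outcome is biased. It is not: the 1-month and 30-day items are clean, and the urine screens essentially so.
- **The 6-month figures.** Sexual behaviour has no 6-month window. For drugs and alcohol the 6-month item is collected, but the abstract does not name it as an outcome window. Its larger shares matter only if it is analysed for change.
- **Lifetime use.** It cannot fall, but the article nowhere says it will be analysed for change. It appears in a list of what the survey asks.
- **A contradiction between sections.** A reader might see one between the abstract and Primary Outcome Variables. The abstract's two windows are both among those the survey collects, so this is mainly a subset, with untidy wording in the parenthesis.
- **Stakes.** This is a single-group pilot of 30 with no stated efficacy threshold, and the Conclusions tie the larger trial to relevance, feasibility and acceptability. A post-to-3-month comparison, where departing pre-intervention weeks could look like a late gain, is not a specified contrast.

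It can also be said that choosing the analysed window is detail for an analysis plan that is not shown. That does not dispose of the point. The article itself fixes the programme length, the survey times, the windows and a change estimate at each assessment, and names 3-month drug use as an outcome. Followed as written, it produces the diluted contrast.

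**Conclusion.** The point holds for the 3-month items (drug and alcohol use, sexual behaviour, partner-type activity) at the immediate post-intervention survey. About 46% of their window is pre-intervention time if that survey comes 49 days after session 1, and 54% to 31% if it comes 42 to 63 days after. An immediate change in rate would then show at roughly half its size. If analysed for change, past-6-month drug and alcohol use is affected more: 65% to 77% at the post survey and about 23% at the 3-month follow-up.

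Two assumptions carry this. The survey timing is inferred, because the article does not state it. The direction towards zero requires stable behaviour before session 1, and the size depends on how quickly any effect sets in.

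The 3-month items are clean at both later follow-ups. The documents do not support a claim that the primary behavioural outcomes as a whole are compromised. This is a limited flaw in one contrast, worth correcting because the correction is nearly free.

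**What to change.** In the Data Analysis Plan, state the recall window used for change at each assessment:

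- **Baseline to post:** the 1-month or 30-day items already collected.
- **3- and 6-month follow-ups:** 3-month items may be used for change here, and only here.
- **Partner-type activity:** asked only over 3 months, so analysed for change only at those two follow-ups unless a 1-month item is added.
- **Past-6-month drug and alcohol use:** for change at the 6-month follow-up only, or not at all.
- **Lifetime use:** a baseline descriptor.

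The cost is a few lines of analysis text and, if early change in partner-type activity is wanted, one added survey item. There is a price in information. Thirty-day counts are sparser than 3-month counts, and at the post survey they cover behaviour during the sessions, so an effect that builds gradually is still partly understated (69% shown under the linear build-up above, against 27% for the 3-month window).

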**Figure 1 figure1:**
[figure not shown]
Young Men’s Adult Identity Monitoring (YM-AIM) main components and outcomes. ART: antiretroviral therapy; PrEP: pre-exposure prophylaxis.

Our initial pilot group of YM-AIM consisted of 36 participants. We collected feedback on the participants’ experiences through postintervention assessments and exit interviews. The findings highlighted that the participants reported wanting and needing ongoing social support after completing the intervention to help them achieve their short-term and long-term goals and to help them maintain positive changes in risky sexual behavior. We learned to update YM-AIM from this formative work and incorporate strategies to create sustained support for participants, specifically by including a mentoring component, as suggested by YM-AIM pilot group participants. This novel mentoring approach is supported by findings that highlight that by introducing youth to new experiences and sharing positive values, mentors can help young people avoid negative behaviors; reduce the risk of delinquency, aggression, and drug use; and lead to increased academic satisfaction and performance [17,18].

Feedback from the pilot testing of YM-AIM suggested the need to further refine YM-AIM to include a mentoring component designed to provide ongoing support and reinforcement of behavior change even after completing the intervention. Therefore, we obtained a second grant from the National Institute on Drug Abuse (grant R34DA044106) to further refine YM-AIM, which included updating the content of the intervention and incorporating activities about new advances in biomedical HIV prevention, namely, PrEP and PEP. This update was necessary to remain current with HIV prevention strategies and resulted in a new HIV prevention intervention named Y2Prevent.

Y2Prevent included three new components: (1) biomedical HIV prevention strategies (ie, PrEP and PEP); (2) HIV and STI testing and HIV care referrals and drug screening and drug treatment referral; and (3) a youth mentoring component through a partnership with the Los Angeles LGBT Center.

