### Y2Prevent Overarching Goals and Specific Aims

The overarching aim of Y2Prevent is to develop a culturally tailored and developmentally appropriate behavioral intervention designed to reduce substance use and risky sexual behaviors among African American YMSM aged 18 to 24 years. The specific aims were as follows: (1) conduct formative research to develop Y2Prevent and refine our assessment measures, (2) finalize Y2Prevent study protocols and consent forms and develop a manual of operations, and (3) pilot test and evaluate Y2Prevent to determine intervention feasibility and acceptability and collect preliminary efficacy data.

Y2Prevent has several key objectives related to African American YMSM, which include promoting resilience; building social skills and assets; increasing skills by recognizing and navigating individual, social, and structural barriers leading to risk; adopting and maintaining protective behaviors such as engaging in safe sex; and using PrEP or PEP and HIV and STI testing services. Intervention outcomes include reductions in drug use, alcohol use, condomless sex, number of sex partners, and an increase in condom use intention, condom use self-efficacy, HIV and STI testing recency and frequency, uptake and adherence of PrEP, and linkage to care.

In this study, we describe the approach used to refine the YM-AIM intervention to bring an additional component (mentoring) and additional content (eg, PrEP). We also discuss the proposed approach to evaluate the feasibility, acceptability, and preliminary efficacy of the new intervention, Y2Prevent.

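### Self-reported HIV/STI testing outcomes do not separate study-provided tests from tests participants seek themselves, so the baseline study test can count as improvement

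*Protocol article*

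**What the plan says.** **Outcome.** Y2Prevent Overarching Goals and Specific Aims lists, among the outcomes expected to increase, "HIV and STI testing recency and frequency, uptake and adherence of PrEP, and linkage to care". The Abstract (Methods) also names testing recency and frequency.

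**Measurement.** Primary Outcome Variables assesses HIV and STI testing with existing scales, which include "self-reported HIV testing history and self-reported HIV status". Under Measures, the survey is given "at baseline; after the intervention; and at 3 months and 6 months following completion of the intervention".

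**Tests supplied by the study.** Primary Outcome Variables states: "Participants will be asked to undergo a rapid test for HIV at baseline and 6-month follow-up assessments". Participants also self-collect rectal specimens for "nucleic acid amplification testing (Hologic) at baseline and at the 6-month follow-up". Tracking and Retention, describing payment, speaks of "4 data collection periods including HIV and STI and substance use screens".

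**Testing as part of the intervention.** The Introduction lists as a new Y2Prevent component "HIV and STI testing and HIV care referrals and drug screening and drug treatment referral".

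**Analysis.** The Data Analysis Plan estimates change from before to after the intervention with generalized linear mixed models and a subject-level random intercept, giving 95% CIs at each follow-up. The 30 participants form three sequential groups, and all of them receive Y2Prevent.

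**The concern.** The study supplies the event that it later counts as changed behaviour. A participant who accepts the baseline test and answers the post-intervention survey truthfully can report a recent test whether or not he has become more inclined to seek one. No comparison group tested on the same schedule is described, so nothing in the analysis removes this contribution.

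The pilot is meant to give preliminary efficacy data, and the Data Analysis Plan says its outcomes will inform later large randomised trials. A change in testing produced by study procedure could be read as an effect on test seeking and carried into that planning.

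**Working it through.** The article gives no expected testing rate, effect size or power for this outcome, so there is no planned figure to reproduce. The check has two parts: when the baseline study test falls inside a look-back window, and how large the resulting rise would be.

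**Inputs from the article**
- Study tests at baseline and 6 months (Primary Outcome Variables).
- Group sessions that "will be held weekly for 7 consecutive weeks" (Tracking and Retention).
- Surveys at baseline, post-intervention, 3 months and 6 months (Measures).
- n = 30 (Data Analysis Plan).

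**Assumptions, not in the article**
- The items count study tests.
- The baseline survey is completed before the baseline test, and the test takes place about when sessions begin.
- Acceptance of the study test is unrelated to earlier testing.
- Participants' own testing rate does not change.
- The 6-month study test comes after the 6-month survey.
- There are no study tests other than those at baseline and 6 months.

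**Step 1. Age of the baseline test at each survey**
- Post-intervention: 7 weeks, 7 / 4.345 = 1.6 months.
- 3 months: 7 + 13 = 20 weeks, 4.6 months.
- 6 months: 7 + 26 = 33 weeks, 7.6 months.

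A window is affected when it is at least as long as the age of the test: about 2, 5 and 8 months respectively. If the baseline test precedes the first session by some weeks, these thresholds lengthen by the same amount.

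**Step 2. Which windows are affected.** For illustration, let own tests follow a Poisson process at r = 1 per year. The share tested in the past w months is then 1 − exp(−w/12). With full uptake of the baseline test and no behaviour change:

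| Window | Baseline | Post | 3 months | 6 months |
|---|---|---|---|---|
| 1 month | 8% | 8% | 8% | 8% |
| 3 months | 22% | 100% | 22% | 22% |
| 6 months | 39% | 100% | 100% | 39% |
| 12 months | 63% | 100% | 100% | 100% |

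In an affected window, the test count rises by one for each person who accepted the baseline test.

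**Step 3. Size at an affected survey.** Let p0 be the share recently tested at baseline and u the uptake of the study test. The follow-up share is u + (1 − u) × p0, so the spurious rise is u × (1 − p0).

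| p0 (assumed) | u = 100% | u = 80% | u = 50% |
|---|---|---|---|
| 20% | 80 points | 64 points | 40 points |
| 40% | 60 points | 48 points | 30 points |
| 60% | 40 points | 32 points | 20 points |

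**Step 4. Time since last test.** This measure has no window, so the baseline test caps it at every follow-up. Under the Poisson illustration its mean is 12/r months at baseline and (12/r) × (1 − exp(−r × t/12)) at t months after the baseline test. For r = 1 and full uptake it falls from 12 months to 1.5 (post), 3.8 (3 months) and 5.6 (6 months).

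**Step 5. With study tests left out.** For a fixed window and an unchanged own-testing rate, the expected change is zero at every survey. For example, with r = 1 and a 6-month window, the share is 39% throughout.

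**The case against.** The strongest reply is that the survey instrument is not shown. The article cites existing scales, and a condensed article need not print item wording, look-back windows or scoring rules. The items may already ask where a test was done. This stands as a limit on certainty and size. It does not remove the point, which is that a stated outcome, measure and procedure collide and the text describes no separation.

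A second reply is that testing is itself a component of Y2Prevent, so a rise in study-provided testing is a legitimate result. It is, as a measure of delivery. It is not evidence that participants adopted and maintained testing, which the Discussion gives as an aim.

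A third is that this is a small pilot reporting estimates with CIs, with no success threshold for testing, and that the later trial is conditioned on relevance, feasibility and acceptability. That limits the consequence. The estimates are still intended to inform later trials.

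Readers might also infer more than the documents support:
- **That the outcomes must improve at every follow-up.** With a 3-month window only the post-intervention survey is affected. With a 1-month window none is. The article gives windows of 1 and 3 months for sexual behaviour but none for testing.
- **That the share tested will reach 100%.** Participants are asked to take the HIV test, so uptake may be lower.
- **That the 6-month test adds to the bias.** It does so only if done before the 6-month survey, and the order is not stated.
- **That Tracking and Retention plainly contradicts Primary Outcome Variables.** The payment sentence can be read as HIV/STI screens at all four assessments. It can also be read as a summary of urine screens at four and HIV/STI tests at two.
- **That a control group would absorb the artefact.** Process Evaluation mentions control conditions in passing, but no control group is described in the design or analysis.

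**Conclusion.** The point holds conditionally. As described, the plan lets the baseline study test enter the self-reported testing outcomes and appear as behaviour change. This requires that the items count study tests and that the baseline survey comes before the baseline test.

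Under those conditions recency and frequency are inflated wherever the window reaches back to baseline, most readily at the post-intervention survey. Time since last test is affected at all three follow-ups. The 20- to 80-point range for the spurious rise comes from assumed baseline shares of 20% to 60% and uptake of 50% to 100%. It is not an estimate from the documents. The matter is worth correcting because the bias is avoidable at little cost, but it does not undermine the pilot's feasibility and acceptability aims.

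**What to change.** 1. Define testing recency and frequency as tests obtained outside the study. Add a clause to the survey items such as 'not counting tests done for Y2Prevent', and score only those tests, with a fixed look-back window.
2. Give each survey before any study test at that assessment, and state this order.
3. Report uptake of study-provided tests separately, as a feasibility or component-delivery measure.
4. Reconcile Tracking and Retention with Primary Outcome Variables, so that it is clear at which assessments HIV/STI screens take place.

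The cost is one added clause in existing items and a scoring rule, with no extra visits. One limitation remains: a participant just tested by the study may put off a test he would otherwise have sought, so outside-only scoring could understate test seeking. Showing study-test uptake beside it lets readers judge this.
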